### Data Analysis and Statistics

In addition to the comparison of the intervention and control conditions, respectively; multi-variable logistic regression model will be used to evaluate the associations between disease severity and socio-demographic variables and outcome measures. Study outcomes will be statistically controlled for a limited number of potentially confounding factors, including the presence of psychoactive medication in the participants' history, age, sex, and whether mechanical ventilation was applied during ICU treatment or not.

As the study includes feasibility as an outcome measure, and as the potential study group may expand in the future, the study sample is yet undetermined. For the feasibility measures, a preliminary aim is to include a convenience sample of at least 40 participants.

All analyses will be performed with an intention-to-treat approach for the total group and stratified for gender and age, since normative data suggest that females have more mental health problems than males, while older individuals have less problems than younger ones.

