## Methods

### Study Population and Setting

The present study will include individuals after intensive care, in two Swedish settings; four ICUs in the Skåne Region (southern Sweden) and two ICUs at Södersjukhuset (Region Stockholm). Surviving individuals admitted to ICU-care are invited to a structured follow-up after 12 months, including self-reported questionnaires regarding mental health problems. The 12-month follow-up measures are carried out through physical (or telephone) follow-up visits (Region Skåne) or through questionnaires sent by regular mail (Stockholm study site). COVID-19 survivors who screen positively for clinical anxiety or depression, defined as a score of ≥8 on either of the two sub-scales within the questionnaire HADS (26), are invited to take part in the study. Eligible individuals will then undergo a structured online clinical diagnostic assessment by a physician experienced in clinical psychiatry. The structured psychiatric medical assessment is guided by the Mini Neuropsychiatric Interview [MINI, (27)]. The MINI interview provides preliminary, structured diagnoses according to the diagnostic manual of the American Psychiatric Association, the DSM-5 [American Psychiatric Association, (28)]. The sections chosen for this assessment include those related to major depression, generalized anxiety disorder, and post-traumatic stress. In addition to the abbreviated MINI assessment, a non-structured clinical interview and broad diagnostic assessment will be performed.

After the assessment, eligible ICU survivors will be offered to enter the study. Consenting participants will be randomized on an equal basis (1:1) to the intervention or control arm. Randomization will be carried out from concealed, opaque envelopes, containing randomization or control assignment as based on a computer-generated randomization list [random.org, (29)], handled by a secretary not involved in the research project. Exclusion criteria, assessed upon the medical examination, include conditions in which participants are acutely suicidal, psychotic, suffering from a mental disorder requiring in-patient psychiatric treatment, opposed to receiving a psycho-therapeutic intervention, or with cognitive problems or language difficulties which are judged to be too extensive for the informed consent procedure and for a psycho-therapeutic intervention.

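### Logistic models for scale-score outcomes, with every analysis repeated by gender and age, lose information and give sparse, often non-estimable stratum results near the only stated sample size

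*Protocol article*

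**What the plan says.** All of the analysis text is in the protocol article, Data Analysis and Statistics.

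- **Model.** Besides the comparison of arms, for which no method is named, a "multi-variable logistic regression model will be used to evaluate the associations between disease severity and socio-demographic variables and outcome measures".
- **Adjustment.** Outcomes are controlled for a small set of factors, "including the presence of psychoactive medication in the participants' history, age, sex, and whether mechanical ventilation was applied during ICU treatment or not".
- **Strata.** "All analyses will be performed with an intention-to-treat approach for the total group and stratified for gender and age". The reason offered is that women report more mental health problems than men, and older people fewer than younger. The number of age groups is not given.
- **Size.** For feasibility, "a preliminary aim is to include a convenience sample of at least 40 participants"; more generally, "as the potential study group may expand in the future, the study sample is yet undetermined".

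The sections Outcomes and Study Variables and Table 1 describe the secondary outcomes as scores: the two HADS subscales, PCL-5, MFIS and the SF-36v2 mental component summary. None has an outcome cut-off. The one HADS threshold (Study Population and Setting) identifies who is invited: a positive screen is "defined as a score of ≥8 on either of the two sub-scales within the questionnaire HADS". The primary outcome, the proportion who consent and stay in the study, is binary.

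**The concern.** Three features do not fit together.

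1. A binary logistic model needs a yes/no outcome, and the secondary outcomes are scores. Using it means cutting the scores at points that the article does not name, and cutting discards information.
2. Women having more symptoms than men, or older people fewer, is a prognostic difference. It is a reason to adjust for sex and age, which the same section already does. It is not a reason to expect the effect of therapy to differ by sex or age, and so does not justify separate analyses.
3. Repeating an adjusted logistic model in subsets of a sample near 40 leaves too few events for the number of terms.

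The article's Conclusions say the results will inform a larger, fully powered trial. Exaggerated odds ratios, or a chance contrast between men and women, could be read as signals and affect that design.

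**Working it through.** **No figure to reproduce.** The 40 is a convenience minimum with no alpha, power, effect size, event rate or dropout behind it. The check is what the planned models can deliver at that size.

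**From the article:** at least 40 participants, allocation 1:1 (about 20 per arm), four named covariates, analyses in the total group and by gender and age.

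**Assumed (not in the article):** outcome rates of 30% and 50% for the event counts. For the simulation: true odds ratio for arm 2.5 (log 0.92), modest covariate effects, 30% women, 70% ventilated, 30% with medication history, and three intercepts (-0.9, -1.7, -2.3) to vary outcome frequency.

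**Step 1: cost of cutting a score.** The most favourable case, a median split of a normal score, keeps 2/π = 0.64 of the information. 40 × 0.64 ≈ 25, so 40 participants act like about 25. The article plans no particular split; this is only an illustration.

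**Step 2: limiting events per term, min(events, non-events)/terms.** Five terms are arm plus four covariates; six adds one severity score.

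| n | Outcome rate | Limiting events | 5 terms | 6 terms |
|---|---|---|---|---|
| 40 | 50% | 20 | 4.0 | 3.3 |
| 40 | 30% | 12 | 2.4 | 2.0 |
| 20 | 50% | 10 | 2.0 | 1.7 |
| 20 | 30% | 6 | 1.2 | 1.0 |

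**Step 3: simulated maximum-likelihood fits.** Separation was tested by linear programming, with 2,000 runs for the total group and 1,000 per stratum size. The total-group model has six terms. Stratum models have five, because sex is constant inside a gender stratum and has to be dropped. For the total group, the mean linear predictor is the intercept + 0.5 × 0.92 + 0.3 × 0.7 + 0.5 × 0.3 + 0.5 × 0.3, that is, the intercept + 0.97. The three settings therefore correspond to outcome rates of roughly 52%, 32% and 21%.

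| Analysis set | Non-estimable, intercept -0.9 | -1.7 | -2.3 |
|---|---|---|---|
| Total, n = 40 | 1.8% | 4.3% | 17.7% |
| Stratum, n = 28 | 6.7% | 18.3% | 37.6% |
| Stratum, n = 20 | 25.1% | 44.0% | 61.6% |
| Stratum, n = 12 | 76.5% | 84.1% | 91.9% |

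Among estimable fits at n = 40, the mean log odds ratio for arm was 1.18 to 1.25, which is 28% to 37% above the true 0.92. The median was 1.07 to 1.10, an odds ratio of about 2.9 to 3.0 against 2.5. The strata of 28 and 12 are the 70% men and 30% women assumed; 20 is an even split.

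**Step 4: would a linear model rescue the strata?** Half-width of the unadjusted 95% interval for a difference in means, in SD units, t × √(2/n per arm):
- 20 per arm: 2.024 × √(2/20) = 0.64
- 6 per arm (12 women): 2.228 × √(2/6) = 1.29

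A linear model can be fitted more often, but a stratum estimate of ±1.29 SD is still uninformative.

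**The case against.** **The sample is not fixed.** The 40 is a preliminary floor for feasibility, and the article allows expansion, so a reader should not take it as the settled size for the regression. That stands. Modest growth would not be enough, though. At 10 limiting events per term (a rule of thumb, taken as an assumption), six terms need 60 events: 120 participants at a 50% outcome rate and 200 at 30%, before any stratification.

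**The logistic model may be meant for binary outcomes.** The article writes only of outcome measures. The feasibility outcome is binary, and cut-offs for the scales may be in a full protocol or analysis plan that is not shown. This also stands: that scores will be dichotomised is an inference. But the wording covers outcome measures generally, and all the symptom outcomes are scores.

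**The HADS threshold.** A reader might infer that 8 or more is useless as an outcome because everyone meets it at entry. The article does not support that. Scores can fall below 8 at follow-up, and someone eligible on one subscale may be below 8 on the other from the start.

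**A very large model.** Table 1 lists six severity descriptors, and a reader might put them all into one model of about ten terms. Nothing in the article says so; it promises a limited number of confounders and names four. Including arm in the logistic model is itself an assumption. The figures above use five or six terms.

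**Counting false positives.** A total number of tests would need a number of age groups and a significance level, and the article gives neither.

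**Conclusion.** The point holds in a limited form. The planned logistic model does not match scale-score outcomes, and repeating all analyses by gender and age is not justified by the reason given and not supportable near 40 participants.

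A reader might conclude that the adjusted logistic model cannot be fitted at all. That is too strong: in the total group it was estimable in about 82% to 98% of simulated trials. The problem there is few events per term (about 2 to 4) and a log odds ratio for arm inflated on average by 28% to 37%. Failure to fit is mainly a problem of the strata. These percentages depend on the assumed rates and effects.

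Two parts need no simulation: sex cannot be a covariate inside a gender stratum, and the stated reason for stratifying argues for the adjustment already planned.

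The point does not touch the feasibility proportion or an unadjusted comparison of arms. It should be corrected, but it does not undermine the pilot's primary aim.

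**What to change.** Change the wording of Data Analysis and Statistics as follows.

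- **Scale outcomes:** linear regression on the continuous follow-up score, adjusted for the baseline score (collected before randomisation under Table 1), arm, age, sex, psychoactive medication history and mechanical ventilation. For the severity question, add at most one severity measure named in advance. That is seven terms and an intercept, leaving 40 - 8 = 32 residual degrees of freedom with complete data. There will be fewer for PCL-5 and MFIS, which Study Variables restricts at 3 months to baseline-positive participants.
- **Feasibility outcome:** keep binary methods.
- **Gender and age:** replace the stratified analyses with the adjustment above. If wanted, give descriptive summaries by sex and age without tests or inferential claims.
- **If a binary version of a scale is wanted as well:** name the cut-off and the time point, and label it supportive.

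The cost is wording only; no data collection changes. The plan gives up separate inferential estimates by sex and age, which a sample near 40 could not support, and examines fewer severity measures in one model.

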### Patient and Public Involvement

Patient organizations have not been directly involved in the design of the present trial. While this is a study protocol, the dissemination and implications of the study results will involve patient and peer-support organizations and public policy makers.

## Discussion

Treatment of mental post-covid syndrome is sparsely addressed in the literature. The demonstration of feasibility for the CBT-ACT intervention in the present study will have potential implications for treatment of many patients with the post-covid syndrome.

### Strengths and Limitations

This project can contribute to improved scientific hypotheses and will provide the base for a future, larger and adequately powered interventional trial in the present research group, as well as in other settings, addressing post-covid mental health symptoms with psycho-therapeutic interventions. The present study thus aims to address feasibility, adherence and participant satisfaction, i.e., to examine how survivors of severe COVID-19 perceive a CBT/ACT intervention which will be tested for the first time. This will add to the current knowledge and be of value in future academic and clinical work.

## Conclusions

This protocol describes a multicenter, randomized, assessor-blinded clinical pilot trial in patients with post-covid mental health problems at 12 months after ICU care. We hope that this pilot trial will be an important contribution to a structured psychiatric assessment of patients with a long-term course of post-covid and strengthen the rationale for future, adequately powered randomized multicenter trials. The addition of evidence for a therapeutic model for critically ill COVID-19 patients with persisting post-covid mental health problems would be beneficial for many patients and for society, and results will be of importance to the design of a larger, fully powered intervention study.

## Ethics Statement

The study was approved by the Swedish Ethics Review Authority (file number 2021/05128, approval date November 3, 2021, and amendments with file number 2021-06977-02 and approval date January 10, 2022, and with file number 2021-01277-02 and approval date March 14, 2022). The study was pre-registered on clinicaltrials.gov (Clinical Trial Identifier number NCT05119608). Feasibility data and early outcome data will give crucial information for future trials on the efficacy of a CBT-ACT intervention in individuals who suffer from long-term anxiety and depression.

